### Sample size

The “steppedwedge” command was used within Stata 16 (StataCorp LLC, College Station, TX, USA) to calculate the minimum detectable difference (MDD) in the main SW-CRT analysis given known parameters. The pre-intervention cholera rate across all clusters was assumed to be 0.4 per 1000 people per month (Table 1). Power was set at 80% with a 5% significance level. The calculation was carried out with the intraclass correlation coefficient (ICC) set at 0.3 and mean cluster size 16,000. ICC, average cluster size and cholera rates were found using the historical data (Table 1). The MDD was 0.1 per 1000, corresponding to a decrease to 0.3 per 1000 people (or increase to 0.5 per 1000) or a 25% reduction in suspected cholera incidence. In a meta-analysis, availability of piped water on premises compared to unimproved water sources was found to reduce the risk of diarrhoeal disease in children by 23% (confidence interval 7–36%) [34].

A sample size calculation for the ITS analysis was also carried out. Follow-up periods of 6 and 12 months from an end date of July 2022 were considered. Mean cholera rates per month were estimated using historical data from the CTC in a quasi-Poisson model with a linear term for year and harmonic terms for month. These were used along with estimates of variance and over dispersion parameters to find the minimum detectable difference. The mean monthly rate per 1000 people was estimated to be 0.25 over a 12 month follow-up, 0.29 over 6 months. The minimum detectable reduction in cholera rates was therefore estimated to be 65% with a follow-up time of 12 months, and 75% for 6 months.

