### Study setting

Uvira is a town of approximately 280,000 inhabitants on the shore of Lake Tanganyika, in Eastern DRC (South Kivu) [47]. The region is characterised by protracted conflict and ethnic violence [48], with at least 100 active armed groups identified in South and North Kivu as of 2019 [49] and continuing, massive population displacements [50].

Cholera has been endemic in the region since the 1970s and Uvira is located within an internationally designated transmission “hotspot” [14, 51]. The CTC located in the General Hospital in Uvira is the main care structure for acute diarrhoea cases—defined as three or more loose or watery stool per day—for the city and provides free treatment including rehydration and, in some cases, antibiotics [21]. CTC admissions have been recorded by the study team since 2009, with an average of 1266 patients admitted annually or 3.4 admissions per year per 1000 inhabitants.

The WHO/UNICEF Joint Monitoring Program estimates that in 2017 approximately 36% of households in DRC relied on unimproved drinking water services and an additional 9% used surface water as their primary source [35]. The existing water supply infrastructure in Uvira was established in the colonial era (1958) [52] and was severely damaged during the First Congo War (1996–1997), with parts then repaired and/or modified by NGOs in the early 2000s. In 2018, before the planned intervention began, the water supply system in Uvira provided a partial and intermittent piped water service that reached an estimated 31% of the population [52]. Surveys conducted by the study team in preparation for the trial in 2016 and 2017 indicated that almost half (47%) of the participants (747 respondents from 458 households) reportedly used surface water—lake (13%) or rivers (34%), about a third (34%) used a tap outside their compound, and 18% had a tap in their compound as primary drinking water source (unpublished data).

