**Fig. 1 Fig1:**
[figure not shown]
Map of Uvira with the definition of clusters and groups: South (blue, *n* = 6) and North (pink, *n* = 10)

**Table 1 Tab1:** Key cluster characteristics

Cluster #	Estimated population (March 2018)	Area [km^2^]	*Mean # suspected cholera cases per month	*Mean monthly incidence per 1000	Existing pipe length [m]	Pipe length to rehabilitate [m]	Length of new pipes to install [m]	# existing household connections	# provisionally planned new household connections	Number of planned new community taps	Allocation sequence
1	4291	2.02	1.9	0.4	2152	57	2628	16	66	6	15
2	4990	0.76	6.0	1.2	1578	1658	1792	89	25	3	16
3	11,183	0.87	6.4	0.6	5574	1266	1864	171	25	7	10
4	7328	1.02	5.4	0.7	2347	0	3398	25	100	5	12
5	13,649	1.27	4.4	0.3	2786	797	4177	19	205	4	9
6	8389	0.48	5.8	0.7	1730	499	2328	43	82	6	13
7	7480	0.37	2.0	0.3	4525	367	1065	152	26	2	8
8	15,455	0.43	4.8	0.3	2961	1097	1793	199	25	5	7
9	3994	0.36	9.4	2.4	3848	189	2446	183	25	8	11
10	14,175	0.59	7.1	0.5	8901	692	1520	525	25	7	1
11	56,106	1.70	14.5	0.3	8775	1599	2401	633	254	16	5
12	12,462	0.99	3.0	0.2	2292	1455	1844	22	193	1	14
13	50,764	2.75	10.4	0.2	17,781	1666	1266	1384	24	11	4
14	16,175	0.55	6.7	0.4	907	0	2549	35	220	5	3
15	15,183	0.81	7.2	0.4	4091	135	2420	161	62	9	2
16	19,338	1.98	10.6	0.6	1788	2061	2874	28	318	20	6
**Mean**	**16,310**	1.06	6.6	0.4**	72,033	13,538	36,363	3685	1675	7.2	–
Minimum	3994	0.36	1.9	0.2	907	0	1065	16	25	1	–
Maximum	56,106	2.75	14.5	2.4	17,781	2061	4177	1384	318	20	–

*Based on CTC admissions between January 1, 2009, and March 31, 2018, and population in March 2018

**Mean weighted by cluster population size

Within each group (South and North), clusters were randomised to different initiation periods by the research team using a random number generator, with the intervention delivered to the South clusters first. The intervention interval—or “step”—during which time a given cluster receives the intervention was planned to be 4 weeks; this interval was extended to up to 8 weeks for the installation of new household connections to the water supply network (Fig. 2)—the reasons are discussed below.

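### The stepped-wedge detectable difference of 25% rests on a flat 2009–2018 rate of 0.4 per 1000 per month; under the decline that the protocol's own trend model forecasts, it is about 29–31%

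*Protocol article*

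**What the plan says.** For the stepped-wedge analysis, the Sample size section states "The pre-intervention cholera rate across all clusters was assumed to be 0.4 per 1000 people per month (Table 1"), with "intraclass correlation coefficient (ICC) set at 0.3 and mean cluster size 16,000". It adds "Power was set at 80% with a 5% significance level", and concludes "The MDD was 0.1 per 1000, corresponding to a decrease to 0.3 per 1000 people", a 25% reduction. The source is given as "ICC, average cluster size and cholera rates were found using the historical data (Table 1"). The footnote to Table 1 defines that source: "Based on CTC admissions between January 1, 2009, and March 31, 2018, and population in March 2018".

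For the ITS, the next paragraph of the same section fits a quasi-Poisson model with a yearly trend and seasonal terms to the treatment-centre history. It projects 6 and 12 months forward from July 2022: "The mean monthly rate per 1000 people was estimated to be 0.25 over a 12 month follow-up, 0.29 over 6 months". The section does not say why one calculation uses the flat average and the other the trend.

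The Analysis plan says that the intervention takes under two years and that each cluster's transition data are left out. Study setting describes a town of about 280,000, "with an average of 1266 patients admitted annually or 3.4 admissions per year per 1000 inhabitants".

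**The concern.** What drives power for a rate is the number of cases expected while the trial runs. The 0.4 averages data centred on about mid-2013, whereas the roll-out falls within the two years or so before July 2022. The team's own model, fitted to the historical admissions, puts the rate well below 0.4 immediately afterwards. Expected suspected cases per cluster-month are 16,000 × 0.4/1000 = 6.4 under the planning rate, against 4.6 at 0.29 and 4.0 at 0.25, which is 28–38% fewer.

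The protocol sets its 25% beside a meta-analytic 23% reduction in childhood diarrhoea (confidence interval 7–36%), so the reader takes the trial to be roughly able to detect the effect it hopes for. If the detectable reduction is nearer 30%, that comparison is less reassuring.

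**Working it through.** **Is 0.4 right as a historical rate?** Table 1 sums to 105.6 cases per month and 260,962 people: 105.6/260,962 × 1000 = 0.405 per 1000 per month. It is.

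**Reproducing the stated MDD.** Inputs from the protocol: 16 clusters with one allocation position each, 16,000 people per cluster, ICC 0.3, 5% significance, 80% power. Assumptions of this check: two-sided test, equal clusters, one cluster per period, each period taken as a month, no overdispersion, variances evaluated at the baseline rate. The model is Hussey–Hughes with fixed period effects, solved by generalised least squares:
- cell variance = λ/16,000
- between-cluster variance = [0.3/(1 − 0.3)] × λ
- MDD = (1.960 + 0.842) × SE of the intervention effect
- power for a 25% reduction = Φ(0.25λ/SE − 1.960)

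MDD per 1000 per month, relative MDD, and power for a 25% reduction:

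| Baseline λ | No transition period excluded | One excluded | Two excluded |
|---|---|---|---|
| 0.40 | 0.0934 (23.3%), 85% | 0.0994 (24.9%), 80% | 0.1060 (26.5%), 75% |
| 0.29 | 0.0795 (27.4%), 72% | 0.0847 (29.2%), 67% | 0.0902 (31.1%), 61% |
| 0.25 | 0.0738 (29.5%), 66% | 0.0786 (31.4%), 61% | 0.0838 (33.5%), 55% |

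The first row reproduces 0.1 per 1000 and 25%, most closely with one transition period excluded. Changing only the rate gives the other rows.

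**Cross-check.** The relative MDD scales close to 1/√λ: 25% × √(0.4/0.29) = 29.4%, and 25% × √(0.4/0.25) = 31.6%.

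**Sensitivity to the model.** Averaging the variance over the two conditions, or reading 0.3 as a coefficient of variation, lowers all the figures: 21.3–26.5% at 0.4, and 24.5–33.5% at 0.25–0.29, over all variants tried. Within each variant the relative MDD rises by a factor of about 1.15 to 1.27.

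**Rate during the roll-out.** The protocol gives none. As an assumption, take a log-linear path from 0.405 in mid-2013 to 0.25 in early 2023. The slope is ln(0.25/0.405)/9.38 = −0.051 per year, which gives 0.284 in mid-2020 and 0.263 at the start of 2022. With one transition period excluded, the MDD is then about 30–31%.

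**The annual rate in Study setting.** 1266/280 = 4.52 per 1000 per year (0.377 per month), and 1266/260.962 = 4.85 (0.404 per month). A rate of 3.4 needs 1266/3.4 = 372 thousand inhabitants, a population stated nowhere. At 0.377 per month, the MDD with one transition period excluded is 25.6%.

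**The case against.** The best defence is that nothing is miscalculated: 0.4 is a correct pre-intervention average, and 25% follows from it. That stands.

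Next, 0.25 and 0.29 are forecasts for after the works, not roll-out rates, and the half-year figure partly reflects season. That also stands, so the consequence is conditional. But the roll-out lies far closer in time to the forecast window than to the data behind 0.4, and the protocol does not explain why a decline assumed for one analysis is left out of the other.

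Third, the denominator behind the forecasts is not given. If it was a projected, larger population, clusters would exceed 16,000 and would recover some of the lost cases. This stands in part. Full recovery of 6.4 cases per cluster-month would need about 22,100 people per cluster at 0.29 or 25,600 at 0.25, a town of about 353,000 to 410,000.

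Fourth, the two analyses cover different periods, so they need not share one rate. Agreed: what is needed is a rate for each period from one model.

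Two stronger readings are tempting, and the documents support neither. A reader might divide 3.4 by 12, get 0.28 per month, and take it as confirmation of a lower baseline. But 3.4 contradicts the 1266 admissions beside it, and the corrected figure supports 0.4. A reader might also hold the absolute MDD at 0.1 and report 34–40% (0.1/0.29 and 0.1/0.25). But the absolute MDD shrinks with the rate, to about 0.08.

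**Conclusion.** The concern holds in conditional form. The stated 25% is right at 0.4 per 1000 per month, but not under the decline that the same section forecasts. If that decline applies during the roll-out, the relative MDD is about 29–31% with one transition period excluded (27–34% with none to two). Power for a 25% reduction is then about 61–67% instead of 80%. In absolute terms the MDD falls from 0.1 to about 0.08 per 1000. These figures rest on cluster size staying at 16,000, the July 2022 end date used for the ITS, and the model assumptions listed with the calculation.

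The consequence is limited: the trial covers the whole town in a fixed set of clusters, so the figure describes sensitivity and sets no recruitment target. The 3.4 per 1000 per year is a separate arithmetic error, with no bearing on the MDD.

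**What to change.** 1. In Sample size, derive the expected rate for the stepped-wedge roll-out window from the existing trend model, with the population denominator that matches it. Restate the MDD at that rate, with a range over 0.25–0.40 per 1000 per month, and say how many transition periods are excluded.
2. Explain in one sentence why the stepped-wedge and ITS rates differ.
3. In Study setting, replace 3.4 with 4.5 per 1000 per year (280,000 inhabitants) or 4.9 (Table 1 total of 260,962), or name the denominator that gives 3.4.

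These are text changes plus a re-run of a calculation whose model already exists. No more patients, clusters or follow-up are needed. The cost is that a stated sensitivity figure probably becomes less favourable.

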### Cross-sectional household surveys

During the inception phase of this study, a household survey was conducted in 2016 and repeated in 2017 (unpublished) to assess household water collection, treatment, storage, and use practices as well as drinking water quality before the intervention. An additional survey using similar questionnaires will be carried out upon completion of the intervention (Fig. 2) to assess whether changes in water service modified households’ water-related habits, including the quantity and source of water used for different purposes, water treatment and storage, and personal and household hygiene practices. Drinking water samples will also be collected from participating households to test for bacterial indicators of water quality (*E. coli* and total coliforms). Five hundred households will be randomly pre-selected across the 16 trial clusters and areas with different levels of access to piped water service post-intervention, using a similar sampling strategy as for the two previous surveys [58].

### Economic evaluation

The economic performance of the intervention will be assessed using cost-effectiveness analysis (CEA) and cost-benefit analysis (CBA). Both will use decision analytic modelling to compare costs and outcomes under the intervention scenario as compared to a “do nothing” scenario, over a 20-year time horizon. The CEA will assess the incremental cost per (i) confirmed case of cholera averted, (ii) CTC admission averted, and (iii) disability-adjusted life year (DALY) averted. These measures exclude the value of the broader outcomes of the intervention beyond infectious disease. Therefore, we will also undertake a CBA that will value health and other outcomes (such as time savings) in monetary terms and calculate a benefit-cost ratio. Cost data for these analyses will come from intervention financial records (capital costs), REGIDESO financial records and interviews (operational costs such as electricity, chemicals and staff), and household surveys (cost-of-illness, travel time to off-plot sources). Outcomes will be estimated from trial records.

### Process evaluation

Assumptions on the pathway from intervention to impact (Fig. 3) will be assessed, if possible, by conducting a process evaluation alongside the trial. Information will be gathered from multiple sources: operational data from the water treatment and pumping stations, as well as billing information and community taps registries, in conjunction with household survey data, will allow us to document water service access and quality in each cluster throughout the project—thus helping understand fidelity and compliance of the planned intervention.

**Fig. 3 Fig3:**
[figure not shown]
Conceptual framework for the Uvira trial

### Recruitment and consent

Recruitment of participants for cholera confirmation will occur continuously at the Uvira CTC, where trained study staff have offered participation to all admitted patients since April 2016. Written informed consent (Additional file 2) will be sought from all participants prior to collection of a rectal swab by trained CTC study staff. For patients under 15 years old, parental consent will be sought for participation in the study.

Recruitment of participants for household surveys will be done by trained enumerators following the random sampling scheme described above. Written informed consent will be obtained from an adult individual (over 18 years old) accepting to participate in the survey on behalf of each household.

### Data management

Anonymised data from the CTC registries will be transferred onto electronic tablets by trained study staff and sent onto a secure, encrypted online server via Open Data Kit (ODK) managed by the London School of Hygiene and Tropical Medicine (LSHTM), with daily back-ups. Regular data accuracy checks will be performed by research team members both online (weekly) and during visits to the study site.

Household survey data will also be collected electronically by trained enumerators using ODK, with encryption, and uploaded onto the same LSHTM-managed server. Daily data quality checks will be performed by research team members during household survey data collection periods so that any issues are addressed in a timely manner.

Authorised research team members will download data onto password-protected computers for analysis. Any identifying information will be stored separately from clinical records.

### Data monitoring

While regular ODK data quality checks will be performed by research team members, no data monitoring board was set up for this trial in view of the nature of the intervention (water supply improvements) and low risk to participants; for the same reason, no interim analyses are planned and stopping guidelines have not been established. Reporting adverse events will be the responsibility of the Principal Investigator.

### Auditing and governance

External audits of the trial are currently not planned. A steering committee was set up with representatives of all study partners, including the Ministry of Health, REGIDESO, funding agencies, and cholera response organisations in DRC to advise on research activities. The steering committee will be updated yearly on progress and challenges.

## Discussion

The Uvira trial is expected to provide a rigorous, comprehensive assessment of water service infrastructure improvements in terms of diarrhoeal disease and cholera incidence, with the potential to inform implementation, design, and investments in future large-scale water supply interventions for cholera and diarrhoeal disease prevention. This investigation is not only unique due to the nature of the intervention (improvements and extension of piped water supply) but also because of the proposed approach and efforts—including confirmation of suspected cholera cases—to enable rigorous research in a complex setting. Beyond the health impact assessment, by documenting research and intervention processes via multiple sources of information, this study is expected to provide insights into which cholera and diarrhoeal disease prevention mechanisms may be most feasible, economically efficient, and effective. Furthermore, the availability of several years of historical cholera and diarrhoeal disease incidence data provides an opportunity to understand long-term disease transmission trends in an endemic context.

Because this research will be conducted in Eastern DRC, in a challenging context not untypical of cholera transmission hotspots, we have adopted a pragmatic approach to mitigate the impact of pre-identified threats to the protocol. This strategy was adopted in response to the inherent instability of the study setting and complexity of this large-scale infrastructure intervention and a recognition that many potential risks would be beyond the control of the study team or indeed the intervention team. Favourable security, political, administrative, and technical conditions, as well as users’ demand for an improved water service, will be necessary to enable the delivery of the intervention as planned and to execute optimally on all aspects of this study protocol. Here we describe a number of pre-identified risks to the intervention and to the study, and discuss how the design features of our pragmatic strategy can mitigate these.

### Context-specific challenges: security, climate, and administrative processes

Several factors may lead to deviations from the planned timeline for the delivery of the intervention. Given the general volatility and ongoing conflicts in South Kivu [48, 49], construction and research activities could be interrupted at any time by security issues. The condition of existing infrastructures and roads, including poor drainage and heavy rains during the rainy season, represent another potential cause of delays and supply chain disruptions that is beyond the control of the study and intervention teams. In April 2020, extreme flooding affected an estimated 86,000 people in Uvira [59] and damaged the water intake for the water supply network, resulting in an immediate interruption of the water service for a duration that remains undetermined at the time of writing. The strict enforcement of border closures with Burundi and Rwanda due to the COVID-19 pandemic since end of March 2020 further complicated the situation. Ensuring the safety of the construction and research teams is a top priority on this project. Any deviations from the study calendar and scheduled intervention roll-out will be documented carefully by the construction, REGIDESO, and study teams so that they can be accounted for in the analysis. For example, the SW-CRT could be analysed as a non-randomised SW trial if the allocation of cluster randomisation was not or incompletely followed. Additionally, should completion of the works become unfeasible in a given cluster, we will work with the construction team ad hoc to avoid unnecessary delays to the intervention and determine how this study protocol may need to be amended depending on the situation.

### Administrative and technical challenges

The intervention is technically complex and several engineering challenges are expected. In addition, administrative delays relating to, for example, shipping and importation of construction materials, are likely. And, at a management level, the project involves multiple actors, with the national utility, REGIDESO, working in partnership with a third-party contractor, and the VF providing technical support and guidance.

With regard to the protocol, the first challenge lay in obtaining reliable information on the existing infrastructure: inaccurate mapping of the existing water (and other) networks could lead to incomplete and/or incorrect identification of leaks, of pipes requiring rehabilitation, of existing pipes’ depth (for connecting new pipes), and of works planning with respect to other networks. Construction of new, critical infrastructure such as the 2000 m^3^ water tank outside the city also involves coordination at multiple levels to ensure compatibility with electrical installations and land use authorisations. Although hydraulic models will be used to design the intervention, unforeseen impacts of structural modifications and/or increased water demand could affect service quality and require localised adjustments.

Furthermore, one important limitation of the intervention is that it does not address electricity shortages, which are the primary cause of intermittent water supply in Uvira. Early assessments deemed potential solar and hydraulic electricity generation unfeasible or economically not sustainable in the Uvira context. In 2019, REGIDESO reports show that electricity was supplied on average 12 h per day and for less than 6 h on at least 4 days per month. Previous research in Uvira established a clear link between water service interruptions and increases in diarrhoeal disease incidence [60], suggesting that it would be critical to improve service continuity. Infrastructural improvements, including increased pumping and storage capacity, may increase the buffering capacity of the network to deliver water in case of short electricity interruptions; however, these modifications are unlikely to ensure continuity or even reliability (availability of water at known times) of the water supply in case of prolonged power cut. Information collected via cross-sectional household surveys and during the process evaluation will allow us to document and assess water service quality in each cluster throughout the project.

